**LIST OF ABBREVIATIONS**

---

|        |                                                                                                                                                                                                     |
|--------|-----------------------------------------------------------------------------------------------------------------------------------------------------------------------------------------------------|
| AAC    | Area Above the Curve                                                                                                                                                                                |
| AE     | Adverse Event                                                                                                                                                                                       |
| ABR    | ABR form, General Assessment and Registration form, is the application form that is required for submission to the accredited Ethics Committee; in Dutch, ABR = Algemene Beoordeling en Registratie |
| AUC    | Area Under the Curve                                                                                                                                                                                |
| BMI    | Body Mass Index                                                                                                                                                                                     |
| BP     | Blood Pressure                                                                                                                                                                                      |
| BrAlc  | Breath Alcohol test                                                                                                                                                                                 |
| CA     | Competent authority (also CCMO)                                                                                                                                                                     |
| CHDR   | Centre for Human Drug Research                                                                                                                                                                      |
| CNS    | Central Nerve System                                                                                                                                                                                |
| CRF    | Case Report Form                                                                                                                                                                                    |
| CRU    | Clinical Research Unit                                                                                                                                                                              |
| CV     | Coefficient of Variation                                                                                                                                                                            |
| EC     | Ethics Committee (also Medical Research Ethics Committee (MREC); in Dutch: Medisch Ethische Toetsing Commissie (METC).                                                                              |
| EEG    | Electroencephalography                                                                                                                                                                              |
| ERP    | Evoked Response Potentials                                                                                                                                                                          |
| EU     | European Union                                                                                                                                                                                      |
| FDA    | Food and Drug Administration                                                                                                                                                                        |
| GCP    | Good Clinical Practice                                                                                                                                                                              |
| HR     | Heart Rate                                                                                                                                                                                          |
| ICH    | International Conference on Harmonization                                                                                                                                                           |
| IES    | Intra-epidermal stimulation                                                                                                                                                                         |
| IESEP  | Intra-epidermal electrical stimulation evoked potentials                                                                                                                                            |
| KSS    | Karolinska Sleepiness Scale                                                                                                                                                                         |
| LEP    | Laser-evoked Potentials                                                                                                                                                                             |
| LS     | Laser Stimulation                                                                                                                                                                                   |
| LSEQ   | Leeds Sleep Evaluation Questionnaire                                                                                                                                                                |
| MedDRA | Medical Dictionary for Regulatory Activities                                                                                                                                                        |
| MMN    | Mismatch Negativity                                                                                                                                                                                 |
| MS     | Mean Speed                                                                                                                                                                                          |
| OTC    | Over The Counter                                                                                                                                                                                    |
| PD     | Pharmacodynamic                                                                                                                                                                                     |
| PDT    | Pain Detection Threshold                                                                                                                                                                            |
| PI     | Principal Investigator                                                                                                                                                                              |
| PT     | Preferred Term                                                                                                                                                                                      |
| PTT    | Pain Pain Tolerance Threshold                                                                                                                                                                       |
| RR     | Respiratory Rate                                                                                                                                                                                    |
| SAE    | Serious Adverse Event                                                                                                                                                                               |
| SAP    | Statistical Analysis Plan                                                                                                                                                                           |
| SCR    | Screening                                                                                                                                                                                           |
| SD     | Standard Deviation                                                                                                                                                                                  |
| SDLP   | Standard Deviation of Lateral Position                                                                                                                                                              |
| SDS    | Standard Deviation of Speed                                                                                                                                                                         |

---

---

|        |                                                                                                             |
|--------|-------------------------------------------------------------------------------------------------------------|
| SEM    | Standard Error of the Mean                                                                                  |
| SOC    | System Organ Class                                                                                          |
| SOP    | Standard Operating Procedure                                                                                |
| UrDrug | Urine Drug screening                                                                                        |
| VAS    | Visual Analogue Scale                                                                                       |
| VEP    | Visual-evoked Potentials                                                                                    |
| WBP    | Personal Data Protection Act; in Dutch: Wet Bescherming Persoonsgegevens                                    |
| WMO    | Medical Research Involving Human Subjects Act; in Dutch: Wet Medisch-wetenschappelijk Onderzoek met Mensen. |

---

## 1 BACKGROUND AND RATIONALE

### 1.1 Context

The assessment of potential sedative effects of new drugs is an important part of the early clinical drug development process. Undesired sedative drug effects may have important consequences, such as an increased risk of traffic accidents. Various methods are used to quantify sedative drug effects [1, 2]. This study assesses the sensitivity of additional measures of sedation, including driving behaviour and brain responses to various sensory and cognitive tasks. The Centre for Human Drug Research (CHDR) aims to further validate these methods by demonstrating that they can detect the effects of sleep deprivation. Additionally, sleep deprivation also affects the perception of pain (e.g., lower pain thresholds). In this study the effects of sleep deprivation on a battery of pain tests will also be determined.

Driving studies have been conducted to assess the effects of fatigue, alcohol, drugs of abuse or pharmaceutical agents on driving performance [3-5]. The first driving studies were closed road tests and a combination of laboratory tests to estimate driving performance [6]. These tests have limitations and do not represent normal driving behaviour, which for example includes dynamic interactions with other drivers. An improved version, the standardised on-the-road highway test, includes about 1 hour driving on the public highway with a constant speed while measuring the lateral position of the car with a camera system [7]. Driving behaviour can be characterised with several parameters, e.g. increased swaying in the driving lane, episodes of lane crossings, and difficulty in maintaining a constant speed [7-9]. A similar task with the same end-points can be performed in a more standardised and safe environment with a driving simulator [10]. This was also noted by the FDA in a recently published guideline, considering driving studies with actual motor vehicles and driving simulators equally for registration purposes [11]. This study will research the effect of sleep deprivation on both on-the-road and simulated driving, using the Green Dino driving simulator. This simulator has previously been used in studies including alcohol, sleep medication, and Huntington patients [12, 13]. Additionally, the relationship between driving- simulation and NeuroCart®, a validated test battery that quantifies a large range of drug-sensitive CNS-functions and that has been sensitive to the effects of sleep deprivation [2] will be assessed.

In a previous sleep deprivation study performed at the CHDR, EEG parameters for drowsiness were less affected than expected [2]. However, the applied EEG method was limited to a 1-minute resting EEG (eyes closed) only and only a limited set of electrodes were included. Other studies observed changes in the power spectrum for specific sites and changes in evoked response potentials (ERP) after sleep deprivation [14-16]. With the present study we want to further explore the relationship between sleep deprivation and a wide range of EEG parameters as well as P300 and mismatch negativity (MMN). In addition to the EEG tests, we want to include simple cognitive tasks to capture the effect of sleep deprivation on the different domains of the brain.

Sleep deprivation is a risk factor for the development of chronic pain. Central sensitization – characterized by an increased sensitivity to pain (i.e. hyperalgesia) – is found in subjects with sleep disturbances [17, 18]. Similarly, multiple studies reported that sleep-deprived subjects respond differently to evoked pain tests in a controlled setting, but is still a topic of discussion as other clinical studies provided conflicting results [19]. This may be explained by the large heterogeneity of study populations and study designs, as not all studies included a wide range of nociceptive modalities [20-23]. The design of the current study provides CHDR with the opportunity to both assess the effects of sleep deprivation on its elaborate battery of evoked pain tests (PainCart® [24]), as well as to validate

the use of sleep deprivation as a tool to induce hyperalgesia. If validated, the latter may be used as a model in drug development to demonstrate effects of centrally acting analgesic compounds.

Moreover, the effect of sleep deprivation on laser-evoked potentials (LEPs) and intra-epidermal electrical stimulation (IES) will also be assessed. For assessing sleep-deprived hyperalgesia (i.e., the increased sensitivity to pain), LEPs will be recorded with EEG after a laser stimulus (LS) is given on a pre-defined area on the volar forearm. Intra-epidermal electrical stimulation (IES) is an experimental method to measure nociceptive detection thresholds using electrical stimulation. Quantification of electrophysiological nociceptive activity can be done simultaneously by using the stimuli as events in evoked potential analysis using EEG recordings. Finally, the effects of sleep deprivation on pain will be assessed psychophysically using the McGill Pain Questionnaire after each individual pain test and LEP.

This study has two goals:

1. To measure sleep deprivation effects with various methods in order to clinically validate these methods, and to correlate the results.
2. To design a pain model based on central sensitisation.

The study is split in two parts, to reduce the risk of contaminating one test's results with effects of the other. The two parts measure the effect of sleep deprivation on:

- A. Cognition and driving behaviour.
- B. Response to evoked potentials and pain sensitization.

## **1.2 Study rationale**

### **1.2.1 Benefit and risk assessment**

There is no benefit for the subjects in this study. The risk of the intervention is negligible. For the on-the-road test are safety precautions taken: a driving instructor has access to dual controls to intervene when needed for safety reasons and the subject is instructed about the possibility to stop the driving test before the planned ending.

### **1.2.2 Study population**

The study consists of two parts (Part A and B). For both parts the population will be 24 healthy male subjects, 23 to 35 years of age. Participants can enrol for either part A, part B or both parts.

### **1.2.3 Study design**

An exploratory single-centre cross-over study in healthy subjects. There is no blinding included because of the nature of the study design. Subjects will be randomized on the order of sleep and sleep deprivation.

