### 6.2 Pharmacodynamic endpoints

#### Part A

#### **Simulated and on the road driving**

- Standard deviation of lateral position (SDLP) (main parameter).
- Number of lane departures.
- Mean speed (MS).
- Standard deviation of speed (SDS).
- Perceived driving quality scale and perceived effort scale.
- Driving quality scale by driving instructor.
- Car driving exploratory biomarkers (drive safety score, head movements, steering wheel).

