### 7.1 Efficacy assessments

#### **On-the-road driving test**

Subjects will participate in validated on-road car driving tests. During these tests several safety precautions are taken to guarantee safety of the subjects and regular traffic. A licensed driving instructor (having access to dual controls) guards the safety of the subject and regular traffic during the test. In case the driving instructor or the subject is of the opinion that it is not safe to start or continue the driving test, the test will be interrupted. Subjects will operate a specially instrumented vehicle over a 55-km primary highway circuit, while maintaining a constant speed (95 km/h) and steady lateral position between the delineated boundaries of the right (slower) traffic lane. The subject will be allowed to deviate from this procedure only in order to overtake a slower vehicle traveling in the same traffic lane. The vehicle's speed and lateral position relative to the lane-lines is continuously recorded. These parameters are digitally sampled at 13 Hz by the MobilEye system (MobilEye Vision Technologies Ltd., Israel). Data is edited, off-line, to remove parts where data are disturbed by extraneous events (eg, passing maneuvers). SDLP (cm), ie, the weaving of the car, is the primary outcome variable. SDLP has been shown to be a sensitive measure to demonstrate dose-dependent differences from placebo for alcohol and psychoactive drugs including anxiolytics, antihistamines, antidepressants, hypnotics and analgesics, and drugs of abuse [4, 7, 25]. Standard Deviation of speed (SDS, km/h) will be a secondary variable. Mean lateral position (MLP, +/- cm), and mean speed (MS, km/h) are control variables. During screening, subjects will participate in a training driving test to become acquainted with the procedures of the driving test.

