#### **Instructor assessment of driving quality**

Immediately after each driving test, the driving instructor will indicate the quality of driving performance during the instructor assessment. The assessment is structured with a matrix where aspects of driving receive a score between 1 and 10 (see appendix 2). The indication 'Not Applicable' will be used if there was no assessment possible of the driving aspect. Comments can be applied in the third column. The assessment will be done by the driving instructor and takes approximately 3 minutes.

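### The blanket waiver of blinding also covers the off-line editing of on-road recordings, where sleep state could be withheld before on-road SDLP is derived

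*Protocol*

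**What the plan says.** Section 1.2.3 of the protocol describes an exploratory crossover with randomised order of the two sleep states, and settles masking in one sentence: "There is no blinding included because of the nature of the study design". It draws no line between roles.

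Section 7.1 (On-the-road driving test) describes the signal processing: "Data is edited, off-line, to remove parts where data are disturbed by extraneous events". The only example given is overtaking. The same section says that "SDLP (cm), ie, the weaving of the car, is the primary outcome variable". It does not say who or what performs the editing, what else counts as a disturbance, or whether sleep state is visible at that point.

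Section 6.2 lists among the Part A endpoints "Driving quality scale by driving instructor". Section 7.1 explains how it is obtained: "The assessment is structured with a matrix where aspects of driving receive a score between 1 and 10". The instructor is also the safety guard: "A licensed driving instructor (having access to dual controls) guards the safety of the subject and regular traffic during the test".

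The only wording that suggests masking is a parenthetical mention of blind data review in section 10.3.2. It concerns quality control of entered data and database listings, and reaches neither rating nor signal editing.

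**The concern.** Subjects obviously know whether they slept. That explains why they are not masked, but not why the person cutting a recording afterwards should know the state. Removing segments from a lane-position trace changes the standard deviation computed from what remains. If the editor knows the state and has latitude over what to remove, expectation can move SDLP in either direction: large excursions may be kept more readily after a sleepless night, or removed more readily as disturbances.

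An error of that kind is systematic. More subjects do not average it out, and neither the mixed model nor the Kenward-Roger degrees of freedom in section 9.9 corrects it. The stake is the first goal in section 1.1, which is to validate these methods by showing that they detect sleep deprivation. A contrast partly produced in editing would count as evidence of sensitivity that the method does not have, and a contrast suppressed in editing would hide sensitivity that it does have.

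**Working it through.** **1. The plan's own figure.** Section 9.3, Part A, gives n = 24, a difference of 3.88 cm, an SD of differences of 6.5 cm, and a paired t-test at two-sided 0.05.
- Noncentrality = 3.88 / 6.5 × √24 = 2.924, with 23 degrees of freedom and a critical t of 2.069.
- Power from the noncentral t = 0.7997, which reproduces the stated 0.80.

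This calculation is for simulator SDLP. The simulator paragraph in 7.1 describes no editing, so the sizing of Part A is untouched.

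**2. Where sleep state is known, and whether it needs to be.**

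| Step | What the protocol fixes | Can state be withheld? |
|---|---|---|
| Subject drives | Not blinded (1.2.3) | No |
| Instructor guards the drive and scores it | Not blinded; dual controls and power to stop (7.1, 7.2.1) | Contestable, see the objection |
| On-road recording edited, then SDLP derived | Not blinded (1.2.3); off-line (7.1) | Yes, the drive is over and a file can be coded |
| Simulator SDLP derived | No editing described (7.1) | No such step |
| Quality control of listings | Called blind (10.3.2) | Later step, does not cover editing |

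Only the third row combines an outcome-forming step, no stated protection and no operational reason to know the state.

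**3. Illustration of scale (assumptions, not estimates).** Suppose that there is no true effect, that editing adds a constant shift b to the on-road contrast, and that the simulator's 6.5 cm applies to the road, for which the protocol gives no SD. The standard error is 6.5 / √24 = 1.327 cm, so an observed difference of 2.069 × 1.327 = 2.745 cm reaches p = 0.05. The noncentrality is b / 6.5 × √24.

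| Assumed shift b | Chance of p<0.05 with no true effect |
|---|---|
| 0 cm | 0.050 |
| 0.5 cm | 0.065 |
| 1.0 cm | 0.112 |
| 1.5 cm | 0.192 |
| 2.0 cm | 0.304 |

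Without borrowing the SD, shifts of 0.1, 0.2, 0.3 and 0.5 SD of the differences give 0.076, 0.156, 0.291 and 0.650. The documents do not show which of these values, if any, applies.

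**The case against.** **The editing may involve no judgement.** The protocol names no editor, and section 9.1 leaves derivation algorithms to the SAP, which is not shown. If software removes overtaking by a fixed rule, sleep state cannot influence the result. This stands, and it is why the point is conditional on a person doing the editing. It does not remove the point: 1.2.3 affirmatively waives blinding for everyone, and access to sleep state while recordings are edited is a matter of study conduct.

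**The study is exploratory.** This lowers the consequence. It does not remove it, because validation is a stated goal.

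**A reader might infer that the instructor should be masked too.** The score is a listed endpoint, both compared sessions start at 09:00, and order is randomised. The documents do not support going that far. The instructor guards safety on a public highway and may stop the drive, so withholding sleep state is a contestable safety trade-off. Masking would also fail in the second period if the same instructor attends both visits, which the protocol leaves open: only the rested state has a 14:00 session, so its presence or absence in period 1 reveals the state in period 2.

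**A reader might also infer that bias enters both sides of the planned correlations.** Section 9.9 correlates changes in cognitive tests, simulated driving and on-road driving. Editing is described only for the on-road recording, and the instructor score is not named there. Nor is detection by an observer the validation question: the Part A objectives in section 2 do not mention instructor ratings.

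**Conclusion.** The point holds as a modest recommendation about one step. On-road SDLP is exposed to observer bias that could be reduced, because the waiver in 1.2.3 extends to the off-line editing and nothing else in the protocol protects that step. This rests on one assumption, that a person does at least part of the editing.

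The size cannot be derived from the documents, and the figures in the working only show how a given shift would act. It would be too strong to say that the main driving parameter as a whole is compromised, since section 6.2 lists SDLP for both tests and only the on-road one is edited. Nor do the documents show that any bias will occur. The instructor's score is an unmasked rating and should be read as such, which is a matter of labelling rather than a reason to change how the drive is supervised.

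**What to change.** In section 1.2.3, replace the single sentence with text to this effect: subjects and the driving instructor are not blinded; whoever edits the on-road recordings is blinded to sleep state.

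In the on-road part of section 7.1, add that each recording carries a code showing neither subject, visit nor sleep state when it is edited, and that the removed segments are locked before the code is linked to state. The code should also hide the start time, because an afternoon drive occurs only in the rested state. If editing is fully automated, say so instead.

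In section 6.2 or the study report, label the instructor's 1-10 score as an unmasked, supportive rating. Leave what the instructor is told, and the instructor's safety role, unchanged.

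The cost is a little file-coding work, with no extra subjects, visits or assessments. There is no benefit if no person takes part in the editing.
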